**Fig. 5 Fig5:**
[figure not shown]
Example screenshots from Health Scout smartphone application

**Table 2 Tab2:** Health Scout mHealth application counseling modules

#	Module description
1	HIV serostatus unknown or no recent HIV test, male or not pregnant female
2	HIV serostatus unknown or no recent HIV test, pregnant female
3	Male, not circumcised
4	HIV+, not in care
5	HIV+, in care, not on antiretroviral therapy (ART)
6	HIV+, on ART
7	HIV+, pregnant
8	Male having condomless sex
9	Female having condomless sex

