### Outcomes

The mLAKE trial has three primary programmatic outcomes (HIV care, ART, and MC coverage), one primary biologic outcome (HIV population viremia prevalence (PVP)), and several secondary outcomes (Table 3). PVP, variously termed community viral load, population viral load, or population prevalence of detectable viremia, was chosen as the primary biologic outcome because it is strongly correlated with HIV incidence [37]. The programmatic outcomes are all key indicators for major HIV service programs and funders.

**Table 3 Tab3:** Descriptions of mHealth Lakefolk Actively Keeping Engaged (mLAKE) trial primary (1°) and secondary (2°) study outcomes^a^

	Outcome	Description	Numerator/event	Denominator
1°	HIV care coverage^b^	Proportion	# linked to HIV care	# HIV-positive
1°	ART coverage^b^	Proportion	# on antiretroviral therapy (ART)	# HIV-positive
1°	MC coverage^b^	Proportion	# non-Muslim men circumcised	All non-Muslim men aged 15–49 years
1°	HIV population viremia prevalence (PVP)	Proportion	HIV+ c VL > 400	All study participants
2°	HIV incidence	Rate	# new HIV infections	HIV-negative person-years
2°	HTS coverage	Proportion	# ever tested and received HIV results	All study participants
2°	ART treatment failure^c^	Proportion	Composite: virologic failure *or* Mortality *or* lost to follow-up *or* stopped ART	# initiated on ART
2°	Consistent condom use^b^	Proportion	# using condoms consistently past 12 months	# sexually active

^a^Outcomes described at the cluster level; outcomes may also be analyzed at the individual level

^b^Self-reported

^c^Outcomes will also be individually analyzed. Virologic failure = any viral load (VL) > 1000 copies/mL. Lost to follow-up = no clinic visit > 180 days

*ART* antiretroviral therapy, *HTS* HIV Testing Services, *MC* male circumcision

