### Sample size/power

The sample size for this trial is fixed. Therefore, the relevant study power-related question was to estimate whether the trial had reasonable chance to detect public health-relevant differences in primary study outcomes, i.e., minimum detectable differences (MDD). Baseline data from a mid-2015 RCCS survey of the fishing community were used to first estimate the coefficients of variation (CV) or intracluster correlation coefficients (ICC) (Table 4). We then used prior data from 9–10/2013 (approximately 18 months prior to the mid-2015 data) to project the expected prevalence of the primary outcomes expected for the control arm at the end of the trial (Table 4). The mLAKE trial is planned for approximately 36 months of follow-up, i.e., two RCCS rounds after the baseline 2015 round. The assumption is that 2013 through 2015 were times of rapid scale-up of CHP service access and that this momentum will slow (roughly by 50% for MC, HIV care and by 75% for PVP, ART, and HIV incidence) over the next 36 months.

**Table 4 Tab4:** Power calculation parameters and derivation of control arm outcome estimates at the end of the trial

Characteristics	CV	ICC	2013	2015	2013 to 2015 ∆	Proposed control arm outcome
Population viremia prevalence (PVP)	0.33	0.02	25%	16%	9%	11.2%
HIV care coverage	0.141	0.061	70%	75%	4.8%	80.1%
ART coverage	0.187	0.072	43%	67%	24.6%	79.7%
MC coverage	0.209	0.062	52%	59%	8.1%	66.9%
HIV incidence	0.929	NA	3.34	2.9	0.44	2.7

*ART* antiretroviral therapy, *MC* male circumcision, *NA* not applicable

MDDs were subsequently calculated with 80% power as described by Hayes and Moulton (Table 5) [39]. Potential impact of contamination was also assessed by assuming 10–50% of control arm residents would be influenced by the intervention. Based upon these calculations, the study should have MDD ratios with 80% power to be able to detect a 41% or greater decrease in PVP, 15% or greater increase in HIV care coverage, 20% or greater increase in ART coverage, and 23% or greater increase in MC coverage. Study power was considered reasonable by the study team for all primary outcomes.

**Table 5 Tab5:** Calculation of minimum detectable difference (MDD) for the mHealth Lakefolk Actively Keeping Engaged (mLAKE) trial

Outcome	Control proportion	% Contamination	Control proportion + contamination	Intervention proportion	MDD ratio	MDD difference
PVP	0.112	0	0.112	0.066	0.593	−0.046
PVP	0.112	0.1	0.107	0.063	0.559	−0.049

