PVP	0.112	0.2	0.101	0.059	0.524	−0.053
PVP	0.112	0.3	0.095	0.054	0.482	−0.058
PVP	0.112	0.4	0.087	0.048	0.433	−0.064
PVP	0.112	0.5	0.077	0.041	0.37	−0.071
HIV care coverage	0.801	0	0.801	0.92	1.149	0.119
HIV care coverage	0.801	0.1	0.814	0.934	1.147	0.12
HIV care coverage	0.801	0.2	0.831	0.952	1.145	0.121
HIV care coverage	0.801	0.3	0.854	0.976	1.144	0.122
HIV care coverage	0.801	0.4	NA	NA	NA	NA
HIV care coverage	0.801	0.5	NA	NA	NA	NA
ART coverage	0.797	0	0.797	0.952	1.195	0.155
ART coverage	0.797	0.1	0.814	0.971	1.193	0.157
ART coverage	0.797	0.2	0.837	0.997	1.191	0.16
ART coverage	0.797	0.3	NA	NA	NA	NA
ART coverage	0.797	0.4	NA	NA	NA	NA
ART coverage	0.797	0.5	NA	NA	NA	NA
MC coverage	0.669	0	0.669	0.822	1.229	0.153
MC coverage	0.669	0.1	0.686	0.842	1.227	0.156
MC coverage	0.669	0.2	0.709	0.869	1.225	0.16
MC coverage	0.669	0.3	0.739	0.904	1.222	0.164
MC coverage	0.669	0.4	0.783	0.955	1.219	0.172
MC coverage	0.669	0.5	NA	NA	NA	NA
HIV incidence	0.027	0	0.027	0.005	0.201	−0.021
HIV incidence	0.027	0.1	0.025	0.005	0.176	−0.022
HIV incidence	0.027	0.2	0.022	0.004	0.146	−0.023
HIV incidence	0.027	0.3	0.02	0.003	0.116	−0.024
HIV incidence	0.027	0.4	0.017	0.002	0.08	−0.025
HIV incidence	0.027	0.5	0.014	0.001	0.05	−0.025

*ART* antiretroviral therapy*, MC* male circumcision, *NA* not applicable*, PVP* population viremia prevalence

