### Participant timeline

Participants were recruited beginning September 2015. As shown in the SPIRIT Figure (Fig. 7), participants will be recruited in an ongoing fashion and followed for two rounds of RCCS or approximately 36 months (usually approximately 18 months between rounds). In-migrating participants can be recruited at any time they are encountered by Health Scouts in an intervention cluster during the study period. Participants can also out-migrate or decline participation at any point in time. Process and qualitative evaluations will be conducted during and after the follow-up period. A cost analysis is planned after trial completion.

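### MC coverage counts circumcisions done before the trial, so the stated 23% detectable increase is roughly a 2.9-fold net gain; an uptake analysis and routine baseline adjustment should be pre-specified

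*Protocol article*

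**What the plan says.** **Outcome.** Table 3 (Outcomes) lists self-reported MC coverage as a primary outcome. The numerator is "non-Muslim men circumcised" and the denominator is "All non-Muslim men aged 15–49 years". Neither is restricted by date of circumcision or by baseline status. The section justifies the programmatic outcomes as indicators used by HIV programs and funders.

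**Who can respond.** Of the nine counseling modules in Table 2, the only one on circumcision is for "Male, not circumcised".

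**Power.** Table 4 (Sample size/power) gives MC coverage of 52% in 2013 and 59% in 2015, a change of 8.1 points, and a projected control-arm value of 66.9%. The text assumes that scale-up slows "roughly by 50% for MC, HIV care and by 75% for PVP, ART, and HIV incidence". Table 5 gives 0.822 as the detectable intervention-arm coverage without contamination. The text summarizes this as a "23% or greater increase in MC coverage" and calls power reasonable for all primary outcomes.

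**Analysis.** Under Statistical methods, each follow-up survey is analyzed separately by logistic GEE. Baseline adjustment is made only if a baseline variable differs between arms at p ≤ 0.1. The allocation was restricted so that the arms differ by no more than 7.5% on baseline MC, among other variables (Randomization).

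**Open population.** Under Participant timeline, "In-migrating participants can be recruited at any time they are encountered by Health Scouts" in an intervention cluster.

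**The concern.** Circumcision is not reversed. A man circumcised before September 2015, or before he moved in, counts as a success in either arm whatever the Health Scouts do. Such men cannot show an effect, but they bring between-cluster variation into the comparison: the CV of 0.209 comes from baseline coverage, which is made up of earlier circumcisions. The relative increase in coverage therefore looks much smaller than the change in behavior needed to produce it.

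At stake is the interpretation of a null MC result. An intervention that doubled the net gain could well be reported as having no effect on MC, and the power section does not show the reader how large an effect the comparison needs.

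**Working it through.** **Inputs.** From the article: 20 clusters per arm, k = 0.209, control proportion 0.669, 80% power, Hayes and Moulton method. Assumed: two-sided alpha of 0.05 (not stated). Cluster size m is also not stated and is back-solved.

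**1. Control projection.** Unrounded 2015 level: 66.9 − 8.1 = 58.8%. Two survey intervals at half the earlier pace: 58.8 + 8.1 × 2 × 0.5 = 66.9%. This reproduces Table 4.

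**2. Table 5.** The formula is

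c = 1 + (1.96 + 0.84)² × [p0(1−p0)/m + p1(1−p1)/m + k²(p0² + p1²)] / (p0−p1)².

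With c = 20, p0 = 0.669 and m = 49, p1 = 0.822, as stated. The same m returns the stated PVP (0.066), HIV care (0.920) and ART (0.952) values.

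The binomial terms sum to (0.2214 + 0.1463)/49 = 0.0075. The between-cluster term is 0.0437 × (0.4476 + 0.6757) = 0.0491. So 0.0491/0.0566, about 87% of the variance, is between clusters.

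**3. Net of the 2015 level.** Control: 66.9 − 58.8 = 8.1 points. Intervention: 82.2 − 58.8 = 23.4 points. Ratio: 23.4/8.1 = 2.89. With the rounded 59%: 7.9 against 23.2, ratio 2.94.

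| Varied | Ratio |
|---|---|
| Baseline 58.5% / 59.5% | 2.82 / 3.07 |
| m = 35 / 107 / infinite (baseline 58.8%) | 2.94 / 2.81 / 2.74 |

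The unknown cluster size hardly matters.

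**4. Power for smaller effects, same formula (m = 49, unadjusted).** For a doubling, p1 = 0.588 + 2 × 0.081 = 0.750. The variance is (0.0083 + 0.0441)/19 = 0.00276, so the SE is 0.0525. Then 0.081/0.0525 − 1.96 = −0.42, and power is 34%. For 1.5-fold it is 12% and for 2.5-fold 62%.

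**5. Allowing for restricted randomization.** The formula ignores the forced balance on baseline MC. Simulation used 22–48 men per cluster, 0–50% turnover and assumed ICCs. Power for a doubling under the planned unadjusted comparison was about 35–60%. At 48 men per cluster, separate runs gave 60–64% with no turnover, 44–45% at 30% turnover and 31–32% at 50%.

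**6. Uptake among men uncircumcised at baseline.** Control uptake under a closed population: 8.1/41.2 = 0.197. About 20 men per cluster is assumed (41% of 49).

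| Assumed ICC | Detectable ratio | Power for a doubling |
|---|---|---|
| 0.02 | 1.56 | 99.5% |
| 0.062 | 1.81 | 90% |
| 0.10 | 2.04 | 78% |

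The ICC would have to reach about 0.21 before the detectable ratio was as large as 2.89. In simulation under the step 5 conditions, power for a doubling was 65–99%, with type I error near 0.05.

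**7. Adjusting coverage for its baseline.** Multiplying the step 2 variance by (1 − r²), where r is the assumed baseline-to-endline cluster correlation, lowers the detectable ratio to about 2.6 at r = 0.5, 2.3 at 0.7 and 2.1 at 0.8 (m = 50). In simulation of uptake of 35% against 19.7% (1.78-fold) with 20–25 men per cluster, unadjusted power was 12–29% over 0–50% turnover. Adjusted power was 79–81% with no turnover, 41–50% at 30% and 28–33% at 50%.

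**The case against.** **Coverage was chosen on purpose.** It is what programs and funders track, the 59% and the 0.822 are both printed, and HIV care and ART coverage also start high. This stands. It is a reason to keep coverage as primary, and no reason to leave the size of the required effect unstated.

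**Much of the lost power comes from the adjustment rule.** This also stands. With no turnover, baseline-adjusted coverage (79–81%) did slightly better than uptake (74–76%) in simulation at 22 men per cluster. The advantage of adjustment fades as turnover rises.

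**An uptake outcome has its own bias risk.** For men absent in 2015 and for in-migrants, both eligibility and event would rest on a recalled date, given after randomization by participants who know their arm. Statistical methods itself notes that individual baseline data are missing for those absent from the baseline survey. This is a sound argument against replacing the primary outcome with uptake in all men. It does not apply to men whose 2015 status is on record, although that status is also self-reported.

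**Stronger readings that the article does not support.**
- A reader might infer that the trial can only detect a near-tripling. The 2.9 is an 80%-power threshold; smaller effects keep some power.
- A reader might infer uptake of 20% against 57% ((82.2 − 58.8)/41.2), or that 88% of control-arm successes (58.8/66.9) pre-date the trial. Both treat the population as closed. If 30–50% of men were newcomers arriving at 45–65% coverage (an assumption; the article gives no figure), the ratio would run from 2.0 to 4.1. For example, half newcomers at 45% put the starting level at 51.9%, so the gains are 15.0 against 30.3 points.

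**Conclusion.** The point holds as a limit on what the MC comparison can show; the outcome definition is not an error. The 80%-power contrast of 66.9% against 82.2% equals about 8 against 23 points of net coverage gain, roughly 2.9-fold. Power for a doubling is about 34% by the plan's own formula and about 35–60% once restricted randomization is allowed for.

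The 2.9 rests on Tables 4 and 5, an assumed two-sided 5% test, and reading net change in an open cohort as new circumcisions. The simulated figures rest further on assumed ICCs, turnover and numbers of men per cluster. The conclusion that an uptake analysis would be more sensitive than the planned unadjusted comparison held across the values tried.

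**What to change.** 1. Keep MC coverage as the registered primary outcome.
2. Before any by-arm data are seen, pre-specify as first secondary outcome MC uptake among non-Muslim men aged 15–49 recorded as uncircumcised in the mid-2015 RCCS. The event is circumcised by the follow-up survey. Use the same logistic GEE, with men analyzed in their baseline cluster. Men not seen at baseline enter only a sensitivity analysis, because their status would rest on a recalled date.
3. Adjust the primary MC coverage analysis for baseline cluster MC coverage in all cases, in place of the p ≤ 0.1 trigger in Statistical methods.
4. In Sample size/power, add that the 23% relative increase is about a 2.9-fold net coverage gain over the 2015 level, and that this reads net change as new circumcisions in an open cohort. Do not enter 57% against 20% as an established uptake figure.

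**Cost.** Wording in the analysis plan and registry; the main uptake analysis uses data the RCCS already collects. It has a smaller denominator (about 41% of men seen at baseline, fewer after out-migration) and says nothing about in-migrants, which is a further reason to keep coverage beside it.

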## Abstract

**Background:**

Effective yet practical strategies are needed to increase engagement in HIV treatment and prevention services, particularly in high-HIV-prevalence hotspots. We designed a community-based intervention called “Health Scouts” to promote uptake and adherence to HIV services in a highly HIV-prevalent fishing community in Rakai, Uganda. Using a situated Information, Motivation, and Behavioral skills theory framework, the intervention consists of community health workers, called Health Scouts, who use motivational interviewing strategies and mobile health tools to promote engagement in HIV treatment and prevention services.

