## Methods/design

### Study setting

The intervention setting is a fishing community (area approximately 2 km^2^, adolescent/adult population approximately 4400) on Lake Victoria in Rakai District in south-central Uganda. Rakai District is bordered to the south by Tanzania and to the east by Lake Victoria. The fishing community is approximately 235 km from Kampala, the capital of Uganda. Since 2011, the Rakai Health Sciences Program (RHSP) has been the primary provider of CHP services in this fishing community. These services include community-based demand generation (e.g., mass media such as radio-talk shows, community meetings, and drama shows), an HIV clinic which provides free pre-ART and ART care, community-based HIV testing, and mobile MC camps. In this community, ART is initiated at time of diagnosis, irrespective of CD4 count (i.e., test and start strategy) as fisherfolk have been designated a key population by the Ugandan Ministry of Health. The HIV prevalence in this community is approximately 40%.

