### Study hypotheses

The study hypotheses are that residents in clusters receiving the Health Scout intervention will have improved HIV service uptake (HIV care, ART, and MC) and decreased HIV population viremia prevalence (PVP) compared to residents in control clusters who do not receive the intervention.

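### ART treatment failure is counted among all ART starters with no minimum time on treatment, so its between-arm comparison can be biased in either direction

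*Protocol article*

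**What the plan says.** Table 3 of the Protocol article (section Outcomes) lists ART treatment failure as a secondary outcome. Its numerator is "Composite: virologic failure *or* Mortality *or* lost to follow-up *or* stopped ART" and its denominator is the number "initiated on ART". Footnote c fixes two of the components: "Virologic failure = any viral load (VL) > 1000 copies/mL" and "Lost to follow-up = no clinic visit > 180 days". The same footnote adds "Outcomes will also be individually analyzed".

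Four other statements bear on who enters that denominator and when:

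- Study hypotheses: residents of intervention clusters "will have improved HIV service uptake (HIV care, ART, and MC"), so ART uptake is meant to rise.
- Study setting: "ART is initiated at time of diagnosis, irrespective of CD4 count", so people start treatment throughout the trial.
- Participant timeline: recruitment is open, and follow-up covers two survey rounds, about 36 months.
- Rakai Community Cohort Study: viral load is assayed in HIV-positive persons at surveys about 18 months apart. The assay is not tied to when a person started ART.

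Statistical methods specifies an intent-to-treat logistic GEE for binary outcomes, run separately at each follow-up survey. Adjustment is triggered only by baseline differences with p ≤ 0.1.

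**The concern.** There are two problems, and each makes the other worse.

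First, with no minimum time on treatment, a high viral load in someone who has only just started counts as treatment failure, although treatment has not yet had time to work.

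Second, membership of the denominator is decided after randomization and depends on arm. If the intervention raises ART uptake, its arm holds a larger share of recent starters. The two groups being compared then differ in time on treatment for a reason that randomization does not balance. Analysing by assigned cluster does not repair this, and neither does adjusting for baseline imbalance. Analysing the components separately does not help either, because the virologic component carries both features.

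This is the listed outcome that describes what happens after ART is started, and the intervention aims "to promote uptake and adherence to HIV services". A misleading result here could hide a real adherence benefit, suggest a harm that does not exist, or show a benefit that does not exist.

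**Working it through.** **Stated figure.** The article gives no rate, power or sample size for ART treatment failure, so there is nothing to reproduce for the outcome itself. The ART coverage shift used below can be checked. The standard formula for comparing proportions in an unmatched cluster trial is

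c = 1 + (z₁ + z₂)² × {[p₀(1−p₀) + p₁(1−p₁)]/m + k²(p₀² + p₁²)} / (p₀ − p₁)²

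Take c = 20 per arm, k = 0.187, p₀ = 0.797 and 80% power (Sample size/power, Tables 4 and 5), with two-sided 0.05 assumed. With m = 50 HIV-positive persons per cluster (assumed) it gives p₁ = 0.952. With m = 43 (107 × 0.40) it gives 0.953. Table 5 states 0.952. This is a minimum detectable value, not a forecast.

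**Inputs**

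- Baseline ART coverage 67% (Table 4, 2015).
- End-of-trial coverage 79.7% in control and 95.2% in intervention (Table 5, no contamination).
- Assumed: failure f = 10% among established users and g = 30% or 50% among recent starters. The article gives neither.
- Assumed: coverage stands in for initiation, the population is closed, and starts are spread evenly over 36 months.

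**Share of ART users who started after baseline**

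- Control: (0.797 − 0.67)/0.797 = 0.159
- Intervention: (0.952 − 0.67)/0.952 = 0.296

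**Failure proportion with no true treatment difference:** F = f + s(g − f), where s is the share of affected starters.

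| Who is affected | g | Control F | Intervention F | Risk ratio |
|---|---|---|---|---|
| Every post-baseline starter (s = 0.159, 0.296) | 50% | 16.4% | 21.8% | 1.33 |
| Every post-baseline starter | 30% | 13.2% | 15.9% | 1.21 |
| Starts in last 6 of 36 months (s = 0.159/6 = 0.027, 0.296/6 = 0.049) | 50% | 11.1% | 12.0% | 1.08 |
| Starts in last 6 of 36 months | 30% | 10.5% | 11.0% | 1.04 |

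The six months only illustrates what recent might mean. It is not a proposed threshold.

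**Direction.** From the formula, F(intervention) − F(control) = (0.296 − 0.159)(g − f). The sign is the sign of g − f. If g = f there is no artefact. If recent starters fail less often, say g = 5% because they have had little time to die, stop or be lost, then F is 0.10 − 0.159 × 0.05 = 9.2% in control and 0.10 − 0.296 × 0.05 = 8.5% in intervention. The intervention then looks better for no reason.

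**A real benefit can be hidden.** Suppose those who would have started anyway fail at 10% in control, and the intervention cuts this by a quarter to 7.5%, while the extra starters fail at 25%. Intervention failure is (0.797 × 0.075 + 0.155 × 0.25)/0.952 = 10.3%, against 10.0% in control. The true reduction does not show.

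**The case against.** A reader might infer that the intervention will necessarily look as if it causes more failure, by a risk ratio of 1.21-1.33. The documents do not support that, for four reasons.

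- **Direction.** Death, loss beyond 180 days and stopping ART accumulate with time on treatment, as does the chance of any high viral load being recorded. Established users therefore have more opportunity to be counted, which pulls the other way.
- **Size.** The larger range treats everyone who started in up to 36 months as if newly started. A viral load taken soon after starting concerns only the last months before a survey.
- **Coverage is not initiation.** Table 3 separates people on ART from people who initiated it. Coverage also rises when fewer people stop. The application has a counseling module for people already on ART, and gains through retention add no starters.
- **Invented rates.** The 30-50% and 10% have no source in the article, and they describe the virologic component rather than the whole composite.

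All four stand, and they limit the claim to a possible bias of uncertain sign.

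Two further arguments carry less weight. One is that viral-load windows are usually left to a statistical analysis plan. Here the article states a rule: it gives loss to follow-up a duration and says any viral load for virologic failure. The point rests on that stated rule and on the stated denominator, not on missing detail. The other is that the primary viremia outcome uses all study participants and ART coverage uses all HIV-positive persons, so a false signal would be read beside sounder results. That limits the consequence but does not make this comparison valid.

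**Conclusion.** The point holds as a possible bias, not a certain one. The outcome counts any viral load above 1000 among everyone who started ART, with no minimum time on treatment, in a group whose make-up the intervention is designed to change. The between-arm difference therefore mixes treatment success with time since ART start, and neither its sign nor its size can be read as an intervention effect.

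Under the assumed failure rates, with the full detectable coverage gain treated as initiations, the spurious risk ratio is about 1.04-1.08 when only late starts are affected. The range 1.21-1.33 is the extreme case in which every post-baseline starter is affected. A smaller coverage gain, or one achieved through retention, would shrink these figures, and the direction reverses if recent starters fail less often than others.

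The outcome is secondary, and the primary viremia outcome does not share the flaw. The change is worth making because it is cheap, but the trial's main conclusions do not depend on it.

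**What to change.** 1. For this outcome, count only viral loads taken after a prespecified minimum time since ART start, the same in both arms.
2. Base the between-arm inference on a group fixed at baseline. One option is participants already on ART at the mid-2015 survey. The other is participants HIV-positive at baseline, with being off ART or having a viral load above 1000 as the event.
3. Report the initiator-based composite descriptively, or by time since ART start.

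The change affects outcome wording and the analysis set, and the surveys already collect the data for the baseline-fixed comparison. The cost is fewer records. In-migrants and people absent from the baseline survey are left out, and the first option also omits new starters. The second option drops death and loss to follow-up as events, so it answers a somewhat different question and overlaps with the primary viremia and ART coverage outcomes.
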